Meeting 17: Conducting the intervention □ [1]	To discuss the positive and negative aspects of the intervention and behavioral changes	- "Compliments board". Knowing that participants have difficulty identifying and recognizing their own qualities, each participant should praise their colleagues, creating a repertoire of positive characteristics of each one	-	Autonomy: emphasis on responsibility Competence: provision of feedback	- Raising the participants’ awareness about the need for advancing in the dynamics involved in the program of physical activities - Reflect with participants on aspects that still need improvement, visualize how to proceed/continue
Meeting 18: Weight training □ [2–5]	To propose a resistance training class, using resources available in the gym (weights and machines)	- Joint warm-up - Dumbbell bench press - Low row - Lateral raise - Dumbbell curl - Triceps on pulley - 45º leg press - Extension and flexor chair - Adductor and abductor chair - Calf raises	- Perform sets of abdominal crunches according to the teacher's instructions	Autonomy: provision of choice Relatedness: involvement and connection	- Favoring that the participant has and perceives option of choice in the conduction of all stages relative to the program of physical activity - Engaging actively in activities, including doing and playing together
Meeting 19: Functional training □ [6, 7]	To offer a meeting focused on activities related to control, stability and motor coordination, contributing to the performance of usual activities	Practice in circuit format: - Joint warm-up - Climber + jump on bench - Abdominal rowing - Support/push-up - Pull-up/inverted crucifix - Dips + lateral raises - Combined exercise - Plyometric - Abdominal plank - Coordination + squat - Juggling + jump rope	-	Autonomy: structural facilitation Competence: facilitation for completing processes relative to goals	- Recognizing the environmental potential for exercising by ensuring multiple potentials - Different conditioning forms of achieving the goals
Meeting 20: Dance □ [8, 9]	To experience different dance practices	- Dance initiation, with samba no pé, samba de gafieira and zouk	-	Competence: provision of challenges	- Creates challenges to break the routine of the exercise sessions, whether for carrying out an exercise in a more challenging manner or carrying out activities in other environments
Meeting 21: Yoga □ [10–13]	To try the basic yoga positions and do a relaxation practice	- Beginners' practice and breathing exercises	-	Autonomy: structural facilitation Competence: provision of encouragement and support	- Adjusting the level of demand for the participants’ capacity to respond to the task - Providing positive feedback to the class and individually, whether recognizing an effort of the participant or complimenting his attitude
Meeting 22: *Slackline* □ [14–16]	To work with different forms of balance through the practice of slackline	- Stretching exercises, individually and in pairs - Balance exercises with bosu and balance platform - Slackline practice, with individual exercises, in pairs, in trios and with everyone	-	Autonomy: orientation with intrinsic objective	- Rationalizing the role of physical activity for reasons such as building a sense of friendship, improvement of skills, energy gain, and a better lifestyle
Meeting 23: Cycling tour □ [14–17]	To practice in groups and outdoors	- Route from UFSC to the seafront	-	Relatedness: involvement and connection	- Valuing group activities
Meeting 24: Sand sports □ [14–16]	To provide a meeting where participants have the opportunity to try beach tennis	Practice at Arena Beach Floripa: - Warm-up - Ball handling drills - Service drills - Moving drills - Mini game	-	Autonomy: structural facilitation Relatedness: cooperation group	- Adjusting the level of demand for the participants’ capacity to respond to the task - Creating groups in virtual environments for experience exchange, facilitating the communication between participants

□: face-to-face meetings; ○: online meetings; 1: Gillison et al. [37]; 2: Bennie et al. [83]; 3: Carneiro et al. [84]; 4: Gordon et al. [85]; 5: Marques et al. [86]; 6: American College of Sports Medicine [59]; 7: Garber et al. [60]; 8: Hellem et al. [87]; 9: Karkou et al. [88]; 10: Breedvelt et al. [89]; 11: Brinsley et al. [90]; 12: Cramer et al. [91] 13: Nanthakumar [92]; 14: Brito et al. [93]; 15: Coventry et al. [94]; 16: Frühauf et al. [95]; 17: Matias et al. [54, 96]

**Table 4 Tab4:** Themes, objectives, dynamics carried out, explored psychological needs, and intervention strategies (week 13 to week 16)

Theme (references)	Objectives	Class dynamics	Take-home dynamics	Psychological needs	Intervention strategies for psychological needs
Meeting 25: Conducting the intervention □ [1]	To discuss the positive and negative aspects of the intervention	- As a form of social interaction, messages are projected in video format, recorded by the participants’ family members, telling a little more about the participant and their perceptions of Vincular Project in the participants’ life	-	Autonomy: provision of justification Autonomy: orientation with intrinsic objective Competence: provision of feedback	- Assessing and reassessing long-term aims - Recognizing internal reasons relative to physical activity, such as satisfaction and pleasure - Recognizing the improvement reached by the participant and remembering the “path” taken to reach it
Meeting 26: Pet day □ [2–4]	To discuss the relationship between animals and people living with depressive symptoms	- Walk with participants’ pets	-	Relatedness: social support Relatedness: involvement and connection	- Encouraging the participant to invite friends and family to carry out/participant in the programs of physical activity - Valuing group activities
Meeting 27: Workers' quality of life and active ageing ○ [5]	To cover content such as assessing the quality of life of the worker, the profile of the work environment and considerations and the importance of leisure, as well as content on guidance for an active lifestyle in old age, maintaining good habits throughout life	- Conversation round	- Fill in the "Well-being Pentacle" and the "Work Environment and Conditions Profile" tools	Autonomy: recognition of the participants’ perspective	- Considering participants’ reasons to exercise, such as preferences, expectations about health outcomes, and the cognitive and affective relationships established in the context of physical activity
Meeting 28: Labour gymnastics □ [6–8]	To talk about the concept and benefits of occupational gymnastics and carrying out different practices	- Stretching practice - Group dynamics - Self-massage and guided relaxation	-	Autonomy: language style	- Opting for language that ensures choice about what to do, such as different types of exercise, about how to adapt the activities
Meeting 29: Talk with [name] ○ [9–11]	To attend the lecture "Quality of life and eating behavior: learning to deal with emotional eating"	- Chat session, with moments of reflection and awareness on the subject of quality of life and eating behavior	- Think about collective activities for the gymkhana	Autonomy: provision of choice Competence: promotion for education	- Favoring that the participant has and perceives option of choice in the conduction of all stages relative to the program of physical activity - Providing educational material containing multidisciplinary information pertinent to the physical activity and health relationship
Meeting 30: Gymnastics for everyone □ [12–14]	To propose gymnastic activities that take into account the different types of bodily manifestations	- Beginners' practices		Autonomy: structural facilitation Competence: provision of encouragement and support	- Adjusting the level of demand for the participants’ capacity to respond to the task - Providing positive feedback to the class and individually, whether recognizing an effort of the participant or complimenting his attitude
Meeting 31: Gymkhana □ [15–17]	To explore collective and competitive activities through activities and games with family and friends	- Equal numbers - Three-legged race - Egg on spoon race - Unscrambling the letters - Emperor penguin - Bridge with hula hoops - Target shooting + balloon popping	-	Competence: facilitation for completing processes relative to goals Relatedness: social support	- Different conditioning forms of achieving the goals - Creating situations that essentially culminate in the participation of family and friends in activities - Encouraging the group`s cohesion in the activities and resolution of problems
Meeting 32: Project closing: trail □ [15–17]	To provide moments of reflection on the trajectory of the intervention and future prospects	Trail on the Costa da Lagoa (Florianópolis/SC)	- Send a statement about your experience with the project, with your perceptions of the issues addressed in the intervention	Autonomy: orientation with intrinsic objective Competence: provision of encouragement and support Relatedness: cooperation group	- Rationalizing the role of physical activity for reasons such as building a sense of friendship, improvement of skills, energy gain, and a better lifestyle - providing positive feedback to the class and individually, whether recognizing an effort of the participant or complimenting his attitude - Creating groups in virtual environments for experience exchange, facilitating the communication between participants

□: face-to-face meetings; ○: online meetings; 1: Gillison et al. [37]; 2: Brooks et al. [97]; 3: Friedman; Krause-Parello [98]; 4: Kamioka et al. [99]; 5: Nahas [55]; 6: Conn et al. [100]; 7: Laux et al. [101]; 8: Serra; Pimenta; Quemelo [102]; 9: Ekinci; Sanlier [103]; 10: Kris-Etherton et al. [104]; 11: Singh et al. [105]; 12: Bento-Soares; Schiavon [106]; 13: Menegaldo; Bortoleto; Mateu [107]; 14: Menegaldo; Bortoleto [108]; 15: Brito et al. [93]; 16: Coventry et al. [94﻿]; 17: Frühauf et al. [95]

The GC, in turn, was expected to continue with its usual activities. However, recognizing the high chance of participants allocated to this group dropping out the research, a decision was made to maintain contact through telephone messages every 2 weeks. The content of these messages included psychoeducational materials on mental health, as well as guidelines for practicing physical activity, reducing sedentary behavior, and improving sleep, which were also shared with individuals who did not meet the eligibility criteria, as mentioned previously (Table 5). It is also worth noting that, if the effectiveness of the intervention is confirmed, the researchers plan to offer the intervention to the control group later, with the goal of extending benefits to all study participants.

**Table 5 Tab5:** Support materials provided to control group participants

Materials	Description	Access
• Physical activity guide for the Brazilian population	• This document presents the first recommendations on physical activity across all life stages, including specific guidelines for pregnant women and individuals with disabilities, tailored to the Brazilian population • It outlines strategies aimed at encouraging a more active lifestyle among the population, thereby promoting health and enhancing quality of life	•https://bvsms.saude.gov.br/bvs/publicacoes/guia_atividade_fisica_populacao_brasileira.pdf
• Support information • "I had a black dog, his name was depression" video	• Contact information for Basic Health Units, Psychosocial Care Centers, facilities offering free or subsidized psychological care in Florianópolis, and other available services • An educational video/short film produced by the World Health Organization, addressing various issues related to depression	•https://sapsi.ufsc.br/files/2021/08/Rede-de-Apoio-SAPSI-7.pdf •https://www.youtube.com/watch?v=XiCrniLQGYc&t=5s
• "Depression: when knowing how to talk and listen inspires life" document	• Created by Janssen and Johnson & Johnson, this material is intended for those who believe that "empathy and acceptance can save lives and make society more humane". The guide addresses several key topics about depression that everyone should be aware of	•https://biblioteca.cofen.gov.br/wp-content/uploads/2021/06/depressao-quando-saber-falar-e-ouvir-inspira-a-vida.pdf
• "How to see the most invisible side of health" video • "The benefits of non-traditional exercises" video	• Videos from the "Autoridade Fitness" channel, available on YouTube • The first video highlights the importance of treating mental health with the same care we give to physical health • The second video offers examples of activities that go beyond the typical gym or weight training routines	•https://www.youtube.com/watch?v=9Asrl9_6FQQ •https://www.youtube.com/watch?v=DsWW9ct17WA
• "WHO guidelines on physical activity and sedentary behaviour" • "Why do cell phones cause significant harm to your spine?" video	• Manual with recommendations on the amount of physical activity (frequency, intensity and duration) required to offer significant health benefits and mitigate health risks • Video from the "Autoridade Fitness" channel, available on YouTube	•https://iris.who.int/bitstream/handle/10665/336656/9789240015128-eng.pdf?sequence=1 •https://www.youtube.com/watch?v=GuCXqBFRiv4
• Sleep hygiene tips • Booklet with guidelines on sleep hygiene • "The danger of lack of sleep in nutrition" video	• Material prepared by the Integrated Health System (SIS) offering tips on sleep hygiene • Booklet with guidelines on sleep hygiene. This material was developed by the Federal Rural University of the Amazon (UFRA) • Video from the "Autoridade Fitness" channel, available on YouTube	•https://www12.senado.leg.br/institucional/sis/noticias-comum/higiene-do-sono-saiba-o-que-e-e-como-ela-pode-melhorar-a-sua-vida •https://repositorio.ufra.edu.br/jspui/bitstream/123456789/1614/1/Cartilha%20%e2%80%9cHigiene%20do%20Sono%e2%80%9d.pdf •https://www.youtube.com/watch?v=Dcl8fjInGjU
• Activity and sleep report • Report interpretation manual	• Report with individual results of accelerometer use, measuring 24-h movement behaviors (physical activity, sedentary behavior and sleep) • Tutorial for interpreting the results of: a) accelerometer usage time; b) moderate to vigorous intensity physical activity; c) total physical activity; d) sleep period; e) sleep efficiency; f) other behavior classifications throughout the day	Unavailable

### Data collection instruments

The initial screening was carried out through an online questionnaire, created on the Google Form® platform, which included basic information to verify the eligibility criteria, as well as application of the Patient Health Questionnaire-9 (PHQ-9) and other screening tools to identify: (a) the need for specialized psychiatric treatment (e.g., psychosis, schizophrenia); (b) the use of antidepressant medication; (c) the requirement for specific treatments targeting depression. This comprehensive approach aimed to efficiently evaluate participants and determine appropriate courses of action based on their responses. The PHQ-9 is designed to evaluate the presence of depressive symptoms through nine questions that address the following aspects: (a) depressed mood; (b) anhedonia (loss of interest or pleasure in doing activities in general); (c) sleep problems; (d) tiredness or lack of energy; (e) change in appetite or weight; (f) feelings of guilt or worthlessness; (g) concentration problems; (h) feelings of sluggishness or restlessness; and (i) suicidal thoughts. The frequency of each symptom in the last 2 weeks is evaluated using a Likert scale ranging from 0 to 3, corresponding to the answers “not at all,” “less than a week,” “a week or more,” and “almost every day,” respectively. Upon completion, the instrument provides a disease severity score from 0 to 27. The questionnaire also includes a tenth question, which, although not contributing to the final score, evaluates the patient’s overall impression of how symptoms impair daily activities, such as work and study, and being associated with the severity of psychiatric symptoms. The validation of this instrument for adults in the general population of Brazil was carried out by Santos and collaborators [109], using a cutoff point of ≥ 9 points to indicate the presence of depression.

Eligible participants subsequently completed a second questionnaire, which incorporated various tools. Although this compilation of instruments was administered online through the Google Form® platform, participants were requested to complete it in the presence of the Vincular Project team, in order to provide assistance when necessary. Some variables were collected using the questionnaire employed in Vigitel telephone surveys, which stands for the Surveillance of Risk and Protective Factors for Chronic Diseases by Telephone Survey, such as (a) sociodemographic information (age, sex, marital status, skin color, and education); (b) behavioral aspects (level of physical activity during leisure time, commuting, domestic, and work); (c) health conditions (from the diagnosis of chronic non-communicable diseases); and (d) self-perceived health. This material was created based on other tools applied by monitoring systems for risk factors for chronic diseases [110, 111] and experiences from system implementation tests carried out in some Brazilian cities [112–114].

The Simple Physical Activity Questionnaire (SIMPAQ), developed and validated by a multidisciplinary group as a clinical instrument to assess physical activity and sedentary behavior in individuals with mental illnesses, was also used [115]. SIMPAQ considers the respondent’s activity over the last 7 days and is structured into five domains, including time spent (a) in bed; (b) in sedentary behavior; (c) walking; (d) doing exercises; and (e) in other activities [115]. Furthermore, another questionnaire was employed to assess the time spent in sedentary behaviors during a typical day of the week and on Sundays in different contexts, such as (a) watching television; (b) using the computer at home; (c) using a cell phone; (d) sitting at work; (e) sitting at school/university; and (f) sitting while traveling by car, motorcycle, or bus [116]. For sleep assessment, the Pittsburgh Sleep Quality Index (PSQI), validated in the adult population of Brazil by Bertolazi et al. [117], was utilized. This instrument evaluates sleep quality over the past month and comprises nine questions, encompassing seven components: (a) subjective sleep quality; (b) sleep latency; (c) sleep duration; (d) habitual sleep efficiency; (e) sleep disorders; (f) use of sleeping medication; and (g) drowsiness and daytime dysfunction. The response options yield a score ranging from 0 to 3, resulting in a total sum of 0 to 21 points. The questionnaire scores can be analyzed as a discrete quantitative variable, with higher scores indicating poorer sleep quality. Alternatively, a cutoff point can be considered, with scores ≤ 5 indicating good sleep quality and scores ≥ 6 signifying poor sleep quality.

For the evaluation of basic psychological needs, the Basic Psychological Needs in Exercise Scale (BPNES), introduced by Vlachopoulos, Ntoumanis, and Smith [118], was utilized. This instrument, translated into Portuguese and adapted for daily activities by Karloh et al. [119], aimed to identify potential changes in the constructs of the Self-Determination Theory following the intervention program. The BPNES is a self-report tool designed to evaluate the extent to which innate needs for autonomy, competence, and relatedness are satisfied in the context of exercise. The questionnaire contains 11 questions with response options ranging from 1 to 5, following the scale “I do not agree,” “I somewhat agree,” “I partially agree,” “I strongly agree,” and “I completely agree,” respectively. The scores are interpreted separately for each basic psychological need, based on the item averages. The perception of barriers to engaging in physical activity was measured using the questionnaire developed by Martins and Petroski [120], which consists of a list of nineteen barriers rated on an ordinal scale, based on the frequency in which the barriers are identified (never = 1; rarely = 2; sometimes = 3; almost always = 4; always = 5). A “perceived barrier” was considered when participants marked the options “always” or “almost always.” Finally, the Fantastic Lifestyle Questionnaire was also administered. Its Brazilian version, translated and validated for young adults, consists of 25 questions divided into nine domains: (a) family and friends; (b) physical activity; (c) nutrition; (d) cigarettes and drugs; (e) alcohol; (f) sleep, seat belts, stress, and safe sex; (g) type of behavior; (h) introspection; and (i) work [121]. The questionnaire employs a Likert scale for answer options. Each question is assigned a specific code, and the sum of points classifies individuals into five categories: (a) excellent (85 to 100 points); (b) very good (70 to 84 points); (c) good (55 to 69 points); (d) regular (35 to 54 points); (e) needs improvement (0 to 34 points) [121].

Participants also used Actigraph GT3X + and wGT3X + accelerometers (ActiGraph Corporation, Pensacola, FL, USA), made available by the Center for Research in Physical Activity and Health (NuPAF), at UFSC, for objective measurement of 24-h movement behaviors. These devices were attached to the non-dominant wrist using an imported PVC bracelet for a continuous 7-day period. Participants followed a 24-h protocol, removing the device only for swimming or water activities involving submersion (but not for other activities with water, such as taking a shower or washing dishes). However, due to the number of devices damaged in the initial collection, participants were instructed to remove the accelerometer during bathing in the second and third collections as a precautionary measure. The data were collected at 30 Hz and the raw acceleration data were utilized. Subsequently, these data underwent a self-calibration process and were converted into the ENMO metric (Euclidean norm minus one), expressed in milligravity units (mg). Further details about the processing of raw accelerometry data can be found in the article by Migueles and colleagues [122]. Thus, the data were analyzed in periods of 5-s epochs and the activities were classified into three categories: (a) sedentary behavior (< 35.6 mg); (b) light physical activity (between 35.6 and 201.4 mg); and (c) moderate to vigorous physical activity (≥ 201.4 mg), adopting the cutoff points of Hildebrand et al. [123, 124]. Sleep duration was estimated using the heuristic algorithm by observing the distribution of change in the Z angle [125]. Participants with at least three valid accelerometer days, comprising two weekdays and one weekend day, each with a minimum duration of 16 h, were included in the analyses. A measurement day was defined as the time interval between wake-up times, accounting for daily cycles that might last more or less than 24 h in total. The accelerometers were programmed and data were downloaded using Actilife software, version 6.8.11, for Windows. Raw data analyses were performed using the GGIR package, version 2.9.5.

The team from Vincular Project was made up of undergraduate, master’s, and doctoral students in the field of physical activity and health. Before the pre-intervention assessment, all team members participated in training to familiarize themselves with the assessment protocols and the application of the questionnaires. All aspects were discussed point by point to ensure procedural standardization. In Table 6, it is possible to verify the schedule of enrolment, interventions, and assessments with details.

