### Exclusion criteria

Require specialized psychiatric treatment, excluding cases of depression (e.g., psychosis, schizophrenia) based on self-reported diagnosis;Exhibit suicidal risk, as indicated by selecting the response options “a week or more” or “almost every day” in the PHQ-9 suicidal risk question;Have illnesses or physical limitations that impede participation in the study.

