### Sample size, randomization, and allocation concealment

The sample size was calculated using G*power 3.1.9.2 software, and was based on an ANOVA model for repeated measures with three time points and two groups. Parameters included an average effect size of 0.25, statistical power of 80%, and 5% significance level for two-tailed tests, reaching a value of 28 individuals. Anticipating a potential dropout rate of up to 50%, the number calculated was doubled, bringing the total sample size to 56 individuals. Eligible individuals were randomly assigned to either the control group (CG), instructed to maintain their usual activities, or the intervention group (IG), which actively participated in the program. To ensure numerical and participant characteristic balance between groups, randomization was stratified by sex, age, and PHQ-9 score, employing a 1:1 ratio. The randomization process was executed using the online platform randomizar.org by researchers not directly involved in the intervention. The allocation list was concealed from all study evaluators.

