### Study variables

The primary outcome of the study was depressive symptoms and secondary outcomes were 24-h movement behaviors (physical activity, sedentary behavior, and sleep) and basic psychological needs (autonomy, competence, and relatedness). Autonomy, competence, and relatedness variables were also examined as potential mediators influencing the effectiveness of the intervention on depressive symptoms. Furthermore, sociodemographic factors, health conditions, self-perceived health, lifestyle, and factors related to the perception of barriers to practicing physical activity were considered as descriptive and/or adjustment variables.

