The limitations of this study must be recognized and addressed in future research. Firstly, the inclusion criteria for the study required participants to have electronic devices, such as computers, tablets, or cell phones, and internet access, as some meetings were conducted online. This could introduce a selection bias, given that access to these technologies in low- and middle-income countries, such as Brazil, is a multifaceted issue involving factors like infrastructure, economy, education, and government policies. Another issue is the exclusion of participants who self-reported the need for specialized psychiatric treatment, based on their self-diagnosis, rather than a formal diagnostic assessment. Furthermore, assessments of biochemical markers that could help elucidate the results, along with an examination of the intervention’s implementation and its cost-effectiveness relationship, were not conducted. Finally, it is crucial to underscore the challenge of ensuring that participants in the CG maintain their usual activities and truly represent a pure CG. This difficulty arises because, in the presence of depressive symptoms, individuals may seek alternative treatments or change their behaviors, such as engaging in physical activity. This is a factor beyond the control of research conducted with this format and proposal.

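### Baseline antidepressant use is identified at screening but named in neither the adjustment list nor the imputation model, although the analysis keeps only intervention attenders and imputes the rest

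*Protocol article*

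**What the plan says.** All references are to the Protocol article.

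- **Data collection instruments.** The online screening form identifies "b) the use of antidepressant medication; (c) the requirement for specific treatments targeting depression". The stated purpose is to "determine appropriate courses of action based on their responses".
- **Exclusion criteria.** One exclusion reads "Require specialized psychiatric treatment, excluding cases of depression (e.g., psychosis, schizophrenia) based on self-reported diagnosis". Cases of depression are thus left out of the psychiatric-treatment exclusion, and no other criterion bars antidepressant users.
- **Sample size, randomization, and allocation concealment.** The text states that "randomization was stratified by sex, age, and PHQ-9 score, employing a 1:1 ratio". The required number is 28, doubled to 56 for a dropout of up to 50%.
- **Study variables.** The article says that "sociodemographic factors, health conditions, self-perceived health, lifestyle, and factors related to the perception of barriers to practicing physical activity were considered as descriptive and/or adjustment" items. Under Data collection instruments, health conditions are described as diagnoses of chronic non-communicable diseases, so that heading does not name medication.
- **Data treatment and statistical analyses.** The per-protocol set keeps intervention participants who continued to the last meeting, attended at least half the meetings overall and in each block, and were assessed at baseline and post-intervention. Control participants need only have been assessed. The analysis called intention-to-treat starts from those same intervention participants plus the controls with both assessments. It fills in everyone else by multiple imputation from sex, age and the variables of interest. The effect analysis is a GEE with time, group and their interaction.

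**The concern.** Antidepressant treatment at entry may be related to how much PHQ-9 changes over 16 weeks, and also to whether a person keeps attending. The article lists its adjustment variables by category and its imputation predictors by name, and this variable is in neither list, although the screening form already holds it.

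Two things are at stake. The smaller is precision: a prognostic baseline variable left out of the model leaves its variance in the error term. The larger comes from the way the analysis sets are built. Intervention participants are selected by attendance and controls are not. Where attendance depends on antidepressant use, those who supply the intervention data have a different mix of users from the arm that was randomised. An imputation model without the variable carries that mix over to the participants being imputed.

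**Working it through.** **1. The plan's own figure.** Repeated-measures ANOVA, within-between interaction, f = 0.25, three times, two groups, alpha 0.05, assuming correlation 0.5 and sphericity (neither is stated): N = 28 gives power 0.812 and N = 26 gives 0.778. This reproduces 28, and 28 / (1 − 0.5) = 56. Neither figure depends on antidepressant use.

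**2. Chance imbalance if randomisation is left intact.** Assume 20–50% users. Under 1:1 allocation (hypergeometric), the SD of the between-arm difference in the proportion of users is 11–14 percentage points at N = 56 and 16–19 points at N = 28. The probability of a difference of at least 20 points is 4–18% at N = 56 and about 17–44% at N = 28. If use shifts PHQ-9 change by an assumed 0.3–0.8 SD, a 20-point imbalance moves the estimate by 0.20 × 0.3 = 0.06 SD to 0.20 × 0.8 = 0.16 SD.

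This is not bias. In a simulation with 40% users (4,000 runs per scenario), the average estimate was unbiased and type I error was 0.049–0.056 unadjusted against 0.048–0.059 adjusted. Power for an assumed 0.8 SD treatment effect:

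| Covariate effect | 28 per arm: unadjusted → adjusted | 14 per arm: unadjusted → adjusted |
|---|---|---|
| 0.3 SD | 0.836 → 0.838 | 0.513 → 0.508 |
| 0.5 SD | 0.817 → 0.827 | 0.511 → 0.516 |
| 0.8 SD | 0.772 → 0.822 | 0.464 → 0.504 |

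**3. Selection by attendance, then imputation.** Let p be the proportion of users in the intervention arm, r1 and r0 the proportions of users and non-users who meet the attendance rule, R = p·r1 + (1 − p)·r0, and b the difference in PHQ-9 change between users and non-users that baseline PHQ-9, sex and age do not explain.

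- Share of users among attenders: p·r1 / R.
- Excess over the randomised arm: p(1 − p)(r1 − r0) / R.
- If imputation ignores use, the completed arm mean takes the attenders' mix, so its bias is b × p(1 − p)(r1 − r0) / R.

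Assume p = 0.40, so p(1 − p) = 0.24, and R = 0.50. This R treats the plan's upper dropout allowance as the fraction failing the rule.

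| r1 − r0 | r1, r0 | Users among attenders | Bias at b = 2 | Bias at b = 4 |
|---|---|---|---|---|
| 0.10 | 0.56, 0.46 | 0.448 | 0.10 | 0.19 |
| 0.20 | 0.62, 0.42 | 0.496 | 0.19 | 0.38 |
| 0.30 | 0.68, 0.38 | 0.544 | 0.29 | 0.58 |

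With R = 0.60 the extremes become 0.24 × 0.10 × 2 / 0.60 = 0.08 and 0.24 × 0.30 × 4 / 0.60 = 0.48. A large-sample check of regression imputation agreed with the table: with use omitted the arm mean was off by these amounts, and with use included the error was essentially zero. The same mix applies to the per-protocol contrast, where no imputation intervenes. The size does not shrink with a larger N. The sign depends on the signs of b and r1 − r0, neither of which the article gives.

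**4. How the covariate must enter the GEE.** With two times and complete data, the time-by-group coefficient is the difference between arms in mean within-person change. A baseline variable entered only as a main effect has the same value at both times and cancels from every change. A numerical check with 28 per arm and an exchangeable correlation confirmed that the coefficient and its standard error were identical with and without the main effect. Adjustment therefore needs an antidepressant-by-time term, or a baseline-adjusted model of the post-intervention score.

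**The case against.** The strongest reply is that this is silence in a condensed article. The Study variables list is given by category and is not declared complete, no GEE covariate is named at all, and exact covariates are commonly settled in an analysis plan that is not shown. The phrase about variables of interest might be stretched to include medication. The screening items also have a coherent purpose of their own, namely triage. Much of this stands, and it keeps the point modest. It does not remove it, because the article does commit itself on imputation predictors and categories of adjustment variable, and neither text names this one.

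Stronger readings are tempting, and the article does not support them:

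- **That chance imbalance feeds directly into the PHQ-9 effect.** Under randomisation the standard error covers it, PHQ-9 is a stratification factor, and the analysis compares change between arms. Step 2 shows nominal type I error and no average bias.
- **That eligibility overlooks depression treatment.** The exclusion criterion expressly leaves depression cases in. That is a stated design choice.
- **That current depression-specific treatment is already on file.** The screening item is a requirement for such treatment, which is not treatment received. Only antidepressant use can be relied on.
- **That baseline status answers the limitation in the Discussion.** The remark that "individuals may seek alternative treatments or change their behaviors, such as engaging in physical activity" concerns what control participants do during the trial. A baseline covariate neither measures nor corrects that.
- **That the listed variables predict PHQ-9 change less well than antidepressant use.** The article offers no evidence for any such ranking.

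Finally, the trial has concluded, so a covariate added now cannot be called prespecified.

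**Conclusion.** The point holds in limited form. Antidepressant use at baseline is identified and such participants are admitted, but the variable is named in neither the adjustment list nor the imputation predictors. For an intact randomised comparison the cost is precision only: 4 to 5 points of power if the variable is strongly prognostic (0.8 SD), and about 1 point or less at 0.3–0.5 SD. For the planned attendance-selected and imputed comparison, omission can bias the intervention mean by roughly 0.1 to 0.6 PHQ-9 points when half the arm is imputed, or 0.1 to 0.5 when 40% is.

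This requires antidepressant use to be related both to attendance and to PHQ-9 change beyond baseline PHQ-9. If either link is absent, the bias is zero. If control missingness depends on use in the same direction, part of it cancels. The prevalence, effect and attendance gap are all assumptions. It is a low-cost improvement to make, and no error in the randomisation or the sample size.

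**What to change.** - Add baseline antidepressant use (yes/no, from the screening form) to the list under Study variables.
- Report it by arm, and again by analysis set, so that readers can see whether attenders differ from those randomised.
- Name it as a predictor in the multiple imputation model.
- Report a PHQ-9 analysis adjusted for it, through an antidepressant-by-time term in the GEE or as a covariate in a baseline-adjusted model of the post-intervention score. A main effect alone would leave the time-by-group estimate unchanged.
- State that these steps were added after data collection.

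Eligibility and randomisation need no change. The cost is a few sentences and one or two degrees of freedom. The expected gain is small if antidepressant use turns out to be only weakly prognostic, and none of this addresses treatment begun after randomisation.
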